#### Efficacy analysis

Although this is a pilot study, we do want to explore whether or not there is a difference between groups. In order to determine differences between those who are randomized to TAU, CRT + FFT, or CRT + TTP, we will conduct a mixed multivariate analysis of variance (MANOVA) with five repeated measures (time: baseline, discharge, 4 weeks post-discharge, 3 months post-discharge, and 6 months post-discharge) as a within-subjects factor and treatment as a three-level between subjects’ factor. We will also evaluate the condition (treatment) × time interaction. We have three quantitative dependent variables: adolescent treatment engagement, post-treatment weight gain, and symptom accommodation. For initial analyses, we will focus on change pre- to 4-week post-discharge. Any post hoc comparisons will involve comparing subsequent assessments to baseline—as they will be simple planned comparisons. This will allow us to retain the most amount of power (i.e., to enable us to reject the false null hypothesis) [57]. We will also set alpha at .10, which will also increase power. Given these parameters, enrolling 60 adolescents would give us an N comparable to prior research using CRT [58].

In addition to the prior analyses, we will also assess developmental trajectories for rate of weight gain post-discharge, treatment engagement post-discharge, and symptom accommodation using latent growth curve modeling (LGCM) with one growth curve analysis for each variable. LGCM is a structural equation modeling method that models repeated observed measures (measured variables) on factors (latent variables) representing random effects [59]. In LGCM, a level factor is used to represent baseline and trend factors are used to represent rate of change across time. Latent variables define the form of rate of change across time (e.g., linear, quadratic, cubic). Factor loadings are fixed to define baseline level and trend. For a linear trend, the factor loadings are set so they increase uniformly with each unit increase in time. Given is a preliminary analysis, these results will allow us to better understand how change occurs over time. Instead of relying on probability values which subject us to increased type II error rates given the small sample size (i.e., low power), we will assess confidence intervals around our estimates to provide information regarding margins of error. All confidence intervals will be 90% confidence intervals given the small sample sizes.

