### Outcomes

The primary aim of the study is to evaluate the feasibility and pilot the procedures for an RCT of CRT with a family component delivered during a hospital stay for medical stabilization. Primary outcomes are as follows:Recruitment rates (% of patients admitted who are eligible, % enrolled). Ideally, we will be able to recruit 30% of those eligible and at least four adolescents and their parents a month.Completion rates (% of those enrolled who complete at least 6 sessions). Completion rates will vary based on the medically dictated hospital stay. As we have no control over when an adolescent will be discharged, completion rates will be combined with enrollment rates to determine how many participants would need to be enrolled in a future study (over-enrollment) to ensure the appropriate number of treatment completers.Refusal rates and reasons whyRetention rate (% of those enrolled who completed all assessment points, rate of drop out over 6 months of follow-up). Ideally, we would have a dropout rate < 25%. As adolescents are discharging to various levels of care, we track dropout rates and determine if we have higher rates associated with certain levels of care (e.g., residential treatment).Average length of time to complete measures

We will also pilot procedures and evaluate the following:Ease of record forms (can the study staff use forms effectively and can the interventionist easily record data needed from each CRT session)CRT task adaptations (e.g., are some tasks more difficult for adolescents, are there modifications that need to be made)Staffing needs (are there enough staff to recruit/enroll/assess/and administer CRT?)Acceptably of RCT to medical staff (evaluated through meetings with and feedback from staff (e.g., physicians, nurses, behavioral health)

In addition to piloting the study and assessing feasibility, our secondary goals are to examine relevant outcomes for a fully powered trial. We will examine the following:Willingness of adolescent to engage in treatment post-dischargeAdolescent rate of weight gain post-discharge to 6 monthsParental accommodation in symptoms post-discharge (group differences and over time changes)Changes in set-shifting or central coherence

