#### Missing data

Every effort will be made to avoid missing data, particularly with respect to our follow-up data points. However, missing data is a common problem in longitudinal research, so it is important to be aware of sources and plan appropriate procedures for accommodating missing data [62]. Missing data can be broadly classified as missing at random or missing not at random and are either ignorable or not ignorable. To assess type of missing data, we will employ various tests for the effects of missing data on our sample (e.g., homogeneity of growth parameters across different patterns of missing data and pattern-mixture modeling). There are several methods for dealing with missing data including ignoring missing data and modeling with complete data only. However, this strategy can bias parameter and standard errors by utilizing smaller proportions of available data and depends on the assumption that data is MCAR [62]. An alternative involves data imputation with multiple imputation [63].

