#### Power analysis

As this is a pilot study, the primary outcome is understanding the feasibility of implementing a large-scale trial. For the mixed MANOVA and using G*power 3.1.7 [64, 65] with three groups (*n* = 20 per group) and five repeated measures, using a 10% probability of a type I error (α = .10), and a medium effect (*f* = .25), the power achieved was .55.

To assess power in the LGCM, we conducted a series of Monte Carlo simulations with 1000 replications, to determine sample size for sufficient power to evaluate developmental trajectories of our primary and secondary outcome variables in a sample of 60 participants with AN. We used M*plus* 7.2 software for all simulations [66]. Population parameter estimates were derived using data from our prior longitudinal analyses. We concluded sufficient power only if the simulation resulted in parameter and standard error bias less than 10% and 15%, respectively, coverage close to 95% (i.e., confidence interval includes the population value), and power above .80 for the significant effects [66–68]. Power calculations were based on ability to detect small but meaningful effect sizes for intercept (baseline level) and trend (rate of change) factors [69]. The results supported low bias (< 10%), acceptable parameter coverage values for the intercept (.95) and trend (.944) factors, and sufficient power (>.95).

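### The five-occasion, three-outcome MANOVA does not fit the measurement schedule, and its power of .55 is a single-outcome figure with no allowance for loss

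*Protocol article*

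**What the plan says.** Under *Efficacy analysis* the article states: "we will conduct a mixed multivariate analysis of variance (MANOVA) with five repeated measures". The time factor is spelled out: "five repeated measures (time: baseline, discharge, 4 weeks post-discharge, 3 months post-discharge, and 6 months post-discharge". Treatment is a three-level between-subjects factor, and the treatment-by-time interaction is also to be evaluated. The three dependent variables are treatment engagement, post-treatment weight gain and symptom accommodation. The first analyses look at change from pre to 4 weeks after discharge, and further comparisons set later assessments against baseline. Separate latent growth curve models, one per outcome, are planned as well.

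Under *Outcomes*, the weight variable is the adolescent's rate of gain from discharge to 6 months. The retention target there is "Ideally, we would have a dropout rate < 25" per cent.

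Under *Power analysis*, the MANOVA figure is computed "with three groups (*n* = 20 per group) and five repeated measures". Alpha is set at .10 and the effect size at f = .25, and the result reported is that "the power achieved was .55".

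Under *Missing data*, the article says of modelling complete data only that "this strategy can bias parameter and standard errors by utilizing smaller proportions of available data" and that it depends on data being missing completely at random. Multiple imputation is then named as an alternative, without being adopted for the MANOVA.

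**The concern.** A repeated-measures MANOVA needs every dependent variable at every level of the time factor. If one outcome is not collected at one level, or is not defined there, the model named in the plan does not exist for that outcome. Someone must then choose, possibly after seeing data, which occasions to drop, which weight variable to use and what reference point to take.

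The power statement raises a related question. It assumes 20 families per arm and five measures each, although the same article accepts some dropout and names three outcomes. The *Discussion* says that trends on the secondary outcomes could help decide whether a larger trial is feasible. The size and definition of these comparisons therefore matter, even though the trial is a feasibility pilot.

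**Working it through.** **Step 1: model against schedule.** Entries are from Table 4. AESED is the accommodation scale. The article does not say which instrument measures engagement; MSCARED (motivational stages of change) is assumed here.

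| Outcome | Baseline (T1) | Discharge (T2) | 4 weeks (T3) | 3 months (T4) | 6 months (T5) |
|---|---|---|---|---|---|
| Engagement (MSCARED, adolescent) | yes | yes | yes | yes | yes |
| Accommodation (AESED, parent) | yes | **no** | yes | yes | yes |
| Current weight | yes | yes | yes | yes | yes |
| Weight gain after discharge | **undefined** | **zero or undefined** | yes | yes | yes |

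Accommodation has four of the five levels by design. Imputation cannot sensibly supply an occasion at which no family is measured. For weight the data exist at all five occasions; the difficulty is the definition. If raw weight is used and compared with baseline, the change includes weight restored in hospital under the nutritional protocol described in *Setting*. The hypothesis in *Secondary aims* concerns gain after discharge.

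**Step 2: reproduce the stated power.** The article does not say which MANOVA effect the figure belongs to. The within-between interaction (Pillai) matches directly:

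- k = 3 groups, m = 5 occasions, N = 60, f = .25, α = .10
- p = m − 1 = 4; h = k − 1 = 2; s = min(p, h) = 2
- df1 = p × h = 8
- df2 = s(N − k − p + s) = 2(60 − 3 − 4 + 2) = 110
- λ = f² × s × N = .0625 × 2 × 60 = 7.5
- Power from the noncentral F = **.551**, which agrees with "the power achieved was .55"

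This is the arm-by-time test of one outcome with 60 complete families. A between-groups test would give .70 at a correlation of .5 between occasions and .57 at .8, so it comes near .55 only with a high assumed correlation. The interaction reading needs no such assumption.

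**Step 3: complete cases only, one outcome, five occasions, equal loss per arm.** Same formula:

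| Loss | N | df2 | λ | Power |
|---|---|---|---|---|
| 0% | 60 | 110 | 7.5 | .551 |
| 10% | 54 | 98 | 6.75 | .505 |
| 15% | 51 | 92 | 6.375 | .481 |
| 20% | 48 | 86 | 6.0 | .457 |
| 25% | 45 | 80 | 5.625 | .432 |

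**Step 4: four occasions (discharge removed), one outcome.** p = 3, df1 = 6. At N = 60, df2 = 112 and power is .606. At N = 45, df2 = 82 and power is .482. At a fixed f, removing an occasion raises the computed power.

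**Step 5: three outcomes in one interaction test, with f = .25 assumed for the joint effect.**

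- Five occasions: p = 3 × 4 = 12, df1 = 24, df2 = 2(60 − 3 − 12 + 2) = 94, power **.342** at N = 60 (.261 at N = 45)
- Four occasions: p = 3 × 3 = 9, df1 = 18, df2 = 100, power .394 at N = 60 (.301 at N = 45)

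**The case against.** The strongest reply is that the trial can perform the analysis behind the .55. MSCARED and current weight are both scheduled at all five occasions, so a single-outcome, five-occasion test is available for engagement and for weight. That stands. A reader might infer that the figure describes no feasible analysis; the schedule does not support this. It is a full-data figure for one outcome.

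A reader might also infer that the missing discharge measurement of accommodation lowers power. It does not: Step 4 gives .606 against .551. The shortfall comes from incomplete families and from applying a one-outcome figure to a three-outcome analysis.

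A third tempting reading is that the plan discards every family with a missed visit. That is how standard MANOVA behaves without imputation, but it is not a rule in the article, which criticises complete-data analysis, names multiple imputation and plans pattern-mixture checks. Leaving the choice of method to a fuller plan is normal for an article. The .43 is therefore conditional on no imputation, and it takes the dropout ceiling as the operating value.

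On weight, discharge is its own time level, so an arm-by-time model of raw weight could separate inpatient from later change. This is correct, but the article names gain as the outcome and sets later assessments against baseline, which does not make that separation.

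Finally, the growth models per outcome already cover part of the remedy, the change from baseline to 4 weeks can be computed for MSCARED and AESED, and efficacy is openly exploratory. These points limit the severity. They do not make the named MANOVA fit its schedule.

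**Conclusion.** The point holds in this form. The time factor under *Efficacy analysis* contradicts Table 4 for accommodation and does not suit the definition of the weight outcome, so the joint three-outcome model cannot be fitted as written. Baseline-anchored weight comparisons would mix inpatient refeeding into a post-discharge outcome.

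The .55 is correct arithmetic for one outcome and 60 complete families, with no allowance for loss. A complete-case five-occasion test has power between .43 and .55 for loss between 25% and 0%. A joint test would have about .34 with no loss.

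These sizes assume that the .55 refers to the interaction, that loss is equal across arms, that nothing is imputed, and that f = .25 carries over to four occasions and to the joint effect. The contradiction with the schedule needs none of these assumptions.

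Severity is should-fix: the primary outcomes are feasibility measures, and the low power is disclosed.

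**What to change.** Replace the MANOVA by one likelihood-based mixed model for repeated measures per outcome. Each should include all randomised families and all available visits, with arm, visit, arm-by-visit and the baseline value as covariate, on the occasions that exist:

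- **Engagement (MSCARED, if confirmed as the measure):** T2 to T5, adjusted for T1.
- **Accommodation (AESED):** T3 to T5, adjusted for T1.
- **Weight:** change or slope from discharge weight (T2) over T3 to T5, adjusted for admission weight.

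Define the first 4-week contrast accordingly, with discharge as the reference for weight.

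Under *Power analysis*, state that .55 is a single-outcome, full-data figure and give power per outcome after expected loss. If the complete-case five-occasion test is kept as the guide, quote the range .43 to .55; otherwise compute the figure for the mixed model.

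The cost is analysis-plan wording and standard software. No new data or visits are needed. The stated power becomes less favourable.

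### The efficacy analysis uses baseline only as an outcome level and as the reference for change, never as a covariate, which gives up precision that data already scheduled could supply

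*Protocol article*

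**What the plan says.** The Efficacy analysis section of the protocol article specifies a mixed MANOVA "with five repeated measures (time: baseline, discharge, 4 weeks post-discharge, 3 months post-discharge, and 6 months post-discharge) as a within-subjects factor", with "treatment as a three-level between subjects’ factor". It adds: "We will also evaluate the condition (treatment) × time interaction". The three dependent variables are adolescent treatment engagement, weight gain after treatment, and symptom accommodation.

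Two sentences fix the comparisons. The first is "For initial analyses, we will focus on change pre- to 4-week post-discharge". The second is "Any post hoc comparisons will involve comparing subsequent assessments to baseline". No covariate is named. The growth-curve model in the same section represents baseline as a latent level factor.

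The Power analysis section takes three groups of 20, five repeated measures and alpha .10, "and a medium effect (*f* = .25), the power achieved was .55".

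Table 4 schedules AESED at baseline, 4 weeks, 3 months and 6 months, but not at discharge. MSCARED, DBS and current weight are scheduled at all five visits. The article does not say which questionnaire carries engagement; MSCARED and DBS are the likely ones.

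**The concern.** In a randomised comparison, a pre-treatment measurement of the outcome is most useful as a covariate. Subtracting it instead forces its coefficient to 1. Whenever the correlation between baseline and follow-up is below 1, that overcorrects, adds noise, and passes chance baseline imbalance into the arm contrast through regression to the mean. With about 20 per arm, such imbalance is to be expected.

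Keeping baseline inside the outcome vector has a second effect. The treatment main effect then averages over an occasion at which, by design, the arms cannot yet differ.

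The stake is modest but real. The plan already raises alpha to .10 and still states power of only .55. The Discussion also says that the absence of any trend between usual care and the experimental groups could weigh against scaling up. A noisier contrast makes a real trend easier to miss.

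**Working it through.** **Inputs from the article.** N = 60 (3 × 20), alpha = .10, f = .25 (Power analysis); hoped-for dropout below 25% (Outcomes).

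**Assumed.** The correlation rho between baseline and follow-up is not given, so a range is shown. f is taken on the raw-score SD, with equal variances at both times.

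**1. The plan's own figure.** The stated .55 reproduces as the multivariate treatment × time interaction:
- 4 time contrasts, 2 group degrees of freedom, s = 2
- df1 = 4 × 2 = 8; df2 = 2 × (60 − 3 − 4 + 2) = 110
- lambda = N·s·f² = 60 × 2 × .0625 = 7.5
- noncentral F power = .551

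**2. The 4-week contrast.** Residual variances, in units of sigma²:
- change score: 2(1 − rho)
- follow-up adjusted for baseline: 1 − rho²

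Their ratio is 2/(1 + rho), which exceeds 1 for every rho below 1. At rho = .5 it is 1.33, so the change score has a third more variance.

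With N·f² = 3.75, lambda is 3.75/[2(1 − rho)] on (2, 57) df for the change score, and 3.75/(1 − rho²) on (2, 56) df for the adjusted analysis.

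| rho | lambda, change | lambda, adjusted | power, change | power, adjusted | gain (points) |
|---|---|---|---|---|---|
| .3 | 2.68 | 4.12 | .398 | .538 | 14.0 |
| .5 | 3.75 | 5.00 | .504 | .612 | 10.8 |
| .7 | 6.25 | 7.35 | .702 | .766 | 6.4 |
| .8 | 9.38 | 10.42 | .855 | .887 | 3.3 |
| .9 | 18.75 | 19.74 | .988 | .991 | 0.3 |

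Gains are taken from unrounded powers. A simulation of 20,000 runs at rho = .5 gave .505 and .602. With 45 analysed (25% lost) and rho = .5, power is .408 and .499.

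**3. The treatment main effect.** With no arm difference at baseline, the five-occasion mean carries (0 + 4 × mean post-baseline effect)/5 = 4/5 of that effect, whatever its shape over time. For AESED, with four occasions, it is (0 + 3 × mean post-baseline effect)/4 = 3/4. Weight gain has no baseline value of its own, so neither fraction applies to it directly. The treatment × time interaction is not diluted in this way, because the baseline level serves there as a contrast.

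**The case against.** The strongest reply is that these are secondary, exploratory analyses in a feasibility pilot, that a change-score contrast is unbiased under randomisation, and that a condensed article may simply omit covariates. The first two parts stand and set the size of the point: it concerns precision only. The third stands in part. A fuller plan could add a covariate, but the article itself puts baseline among the outcome levels and makes it the reference for comparisons, so this is more than silence.

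The gain also depends on an unknown correlation, which need not be the same for engagement, weight and accommodation. At .8 or above little is gained.

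The covariate is not wholly clean either. The Measurement strategy section allows self-report to be completed after randomisation. That weakens any adjusted analysis using such a value, but a change score subtracts the same value in full, so it is no defence of the change score.

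Several stronger readings are tempting and not supported:
- A reader might infer that the plan contradicts its own remark about retaining power. In context, that remark follows the restriction to a few simple planned comparisons. It makes no claim about change scores against covariate adjustment.
- A reader might infer that the 90% intervals would narrow. They are introduced for the growth-curve model, which this change does not touch.
- At rho = .5 with a constant effect, the five-occasion mean has power .527, and the four later occasions adjusted for baseline have .875. That gap merges dropping baseline (.685) with adjusting for it (.875). The main effect is also neither the 4-week focus nor the test behind .55. The mean post-baseline change from baseline already reaches .685.
- A reader might extend the point to cognition. The Outcomes section lists "Changes in set-shifting or central coherence", but that names an outcome rather than an analysis, and it is not one of the three dependent variables.

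**Conclusion.** The point holds as a worthwhile, nearly free gain in precision. For the 4-week contrast at the plan's N, alpha and f, baseline adjustment adds about 14 points of power at rho = .3, 11 at .5, 6 at .7, 3 at .8 and almost none at .9. This rests on f being defined on the raw-score SD, equal variances over time, and a correlation the article does not give. The gain should not be added to the stated .55, which belongs to a different test.

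The dilution to 4/5 (3/4 for AESED) affects the treatment main effect only.

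One ambiguity remains. 'Pre-' in the 4-week sentence could mean the pre-discharge visit instead of baseline. For AESED it can only mean baseline, since nothing is collected at discharge; for engagement and weight it could mean either. The separate sentence on later comparisons names baseline explicitly, so the point does not depend on how this is resolved.

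**What to change.** For each of the three efficacy outcomes, take baseline out of the outcome vector. Model the post-randomisation values, 4 weeks first, on treatment, visit and treatment × visit, with the participant's own baseline value as covariate. This replaces the change-from-baseline comparison.

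For post-discharge weight, use discharge weight as covariate, since that is where the outcome interval starts. Discharge weight is itself measured after the in-hospital intervention, so say so and show the result with admission weight alongside.

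State whether 'pre-' means baseline or the pre-discharge visit. Flag any baseline questionnaire completed after randomisation and repeat the analysis without those values.

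The cost is a change of wording, one degree of freedom per outcome, and simple handling of missing or post-randomisation baselines. No new data are needed.

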#### Secondary aims

The secondary aims are to gather preliminary evidence as to whether or not CRT with parent involvement reduces symptom accommodation by parents, increases adolescents’ willingness to engage in treatment, and increases rate of weight gain *post-hospitalization*. As a traditional outcome of CRT, changes in cognitive flexibility will also be assessed. We anticipate adolescents in the CRT conditions will have greater treatment engagement upon discharge and will have an increase in cognitive flexibility at 6-month follow-up. We further hypothesize that parents in the TTP condition will demonstrate less accommodation of symptoms at 3- and 6-months post-discharge. Finally, we hypothesize that adolescents in the TTP condition will have greater rate of weight gain post-discharge than adolescents in the FFT condition and that adolescents in both CRT conditions will have greater rate of weight gain in comparison with the adolescents in the treatment as usual condition. Given that this is a pilot study, we know that full exploration of these hypotheses will be limited. However, these are the hypotheses we plan on testing in a fully powered trial.

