### Study design

This is a pilot and feasibility study for a randomized controlled trial that is prospective in nature and pragmatic in its approach. The study uses a randomized, three-group design (control, experimental, and contact control) with five assessment time points: baseline (upon admission to hospital for medical stabilization), pre-discharge (the day of, or the day before they leave the hospital), 4 weeks post-discharge, 3 months post-discharge, and 6 months post-discharge. Figure 1 outlines the study flowchart and timetable for data collection.

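### For weight, the stated contrasts start at admission although the outcome is gain after discharge, so read literally they measure total gain including inpatient refeeding

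*Protocol article*

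**What the plan says.** **The outcome.** Outcomes lists the adolescent's rate of weight gain from discharge to 6 months. Secondary aims gives the matching hypothesis: "adolescents in the TTP condition will have greater rate of weight gain post-discharge than adolescents in the FFT condition", with both CRT arms expected to exceed treatment as usual, again after discharge.

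**The time points.** Study design separates two inpatient assessments: "baseline (upon admission to hospital for medical stabilization)" and "pre-discharge (the day of, or the day before they leave the hospital)".

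**The analysis.** Efficacy analysis specifies a mixed MANOVA with "five repeated measures (time: baseline, discharge, 4 weeks post-discharge, 3 months post-discharge, and 6 months post-discharge)". The dependent variables are "adolescent treatment engagement, post-treatment weight gain, and symptom accommodation". It adds "For initial analyses, we will focus on change pre- to 4-week post-discharge" and then "Any post hoc comparisons will involve comparing subsequent assessments to baseline". The growth model is introduced for, among other variables, rate of weight gain after discharge, and its description says "In LGCM, a level factor is used to represent baseline".

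**The data.** Table 4 schedules current weight by chart review at baseline, discharge, 4 weeks, 3 months and 6 months. Setting states that admitted patients follow the unit's nutritional rehabilitation protocol. The description of the intervention gives a median stay of 10 days. The document never names discharge weight as the reference for post-discharge gain.

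**The concern.** The outcome starts at discharge, but the stated reference for comparisons is admission. Patients are being refed between those two points, so a change from admission is inpatient gain plus outpatient gain. That is a legitimate quantity, but it is not the one hypothesised. The variable named as gain after treatment also has no value at the admission level of a five-level time factor, so the model as worded does not fit its own outcome.

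Two things are at stake. The estimate answers a different question from the stated aim. It may also carry extra variance from inpatient feeding and length of stay, although the section justifies its comparisons as preserving power. The Discussion says that trends on the secondary outcomes could inform whether to scale up, so the weight estimate should mean what the aim says it means.

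**Working it through.** **1. The plan's own figure.** Power analysis states .55 for three groups of 20, five measures, f = .25 and alpha = .10. For the MANOVA group-by-time interaction (Pillai):

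- s = min(2, 4) = 2
- df1 = 2 × 4 = 8
- df2 = 2 × (60 − 3 − 4 + 2) = 110
- λ = 0.25² × 60 × 2 = 7.5
- power = .551

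The figure reproduces. It does not depend on which occasion is the reference.

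**2. Does admission-anchored change equal the outcome?** Write I for gain from baseline to discharge and P for gain from discharge to a follow-up visit.

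- Outcome as defined: P (as a rate).
- Contrast as worded: I + P.
- Arm difference: mean(P) difference + mean(I) difference.

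If mean I is the same in all arms, it cancels and the arm difference in kg is unchanged. What remains is the effect on variance: Var(I + P) = SD_P² × (1 + r² + 2cr), where r = SD_I / SD_P and c is the correlation of I and P.

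**3. Share of the interval.** At the median stay, 10 of the 10 + 28 = 38 days from admission to 4 weeks after discharge are inpatient. If the inpatient daily rate is k times the later rate (k assumed; the document gives no rates), the inpatient share of total gain is 10k / (10k + 28):

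| k | Share |
|---|---|
| 1 | 26% |
| 2 | 42% |
| 3 | 52% |

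These shares show how far the measured quantity departs from the defined one. They are not a bias in the arm contrast.

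**4. Possible power loss.** Assumptions: d = 0.5 on P, both CRT arms pooled against usual care (40 v 20), two-sided alpha .10, c = 0. Then d_eff = 0.5 / √(1 + r²), and power comes from the noncentral t with 58 df:

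| r | d_eff | Power |
|---|---|---|
| 0 (from discharge) | .500 | .56 |
| 0.25 | .485 | .54 |
| 0.5 | .447 | .49 |
| 1 | .354 | .36 |

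The result is sensitive to c. With r = 1 and c = −0.5 the variance factor is 1 + 1 − 1 = 1, and there is no loss at all.

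**5. The growth model.** Suppose a straight line in elapsed weeks is fitted through all five occasions, with an inpatient stay of 10/7 weeks and assumed inpatient gain of 0.5 to 2.0 kg/week. A true post-discharge slope of 0.25 kg/week is then estimated as 0.257 to 0.297, and a true slope of 1.0 as 0.987 to 1.027. The distortion is small, because the 26 weeks after discharge dominate the line.

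**6. Cost of dropping the admission occasion.** With four waves, df1 = 6, df2 = 2 × (60 − 3 − 3 + 2) = 112 and λ = 7.5, giving power .606 against .551. The rise comes only from fewer numerator degrees of freedom at a fixed f; it shows that dropping the occasion does no harm on the plan's own calculation.

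**The case against.** A reader might infer that every weight analysis is anchored at admission, that the growth model forces one slope through the inpatient and outpatient phases, and that refeeding gain dilutes the treatment effect. The document does not support that much.

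- **The initial contrast is ambiguous.** Study design calls the discharge assessment pre-discharge, so "For initial analyses, we will focus on change pre- to 4-week post-discharge" can be read as discharge to 4 weeks, which would be right for weight. It can equally mean pre-treatment. The text does not settle it.
- **The growth-model sentence is a general description of the method.** The modelled variable is named as post-discharge gain, no loadings are listed for weight, and curved forms are allowed. The choice of time zero is detail an article may leave to a fuller plan. Step 5 shows that little would follow in any case.
- **Common gain cancels.** It cannot shrink the arm difference in kg; only variance is at issue, and its size rests on an SD ratio and a correlation that the document does not give.
- **The post hoc sentence covers three outcomes.** The accommodation scale (AESED) is not scheduled at discharge, so baseline is its only reference before discharge. The wording looks general, not like a deliberate choice for weight.
- **Admission is a valid randomised origin.** Discharge weight and timing are post-randomisation, so moving the origin has a price.
- **Stakes are limited.** Weight is a secondary outcome in a feasibility pilot.

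All of this narrows the point. The conflict remains: baseline is a defined term meaning admission, the five-level time factor and the post hoc comparisons both use it, and weight is not exempted. The label of gain after treatment does not resolve this, because such a variable cannot be compared with an admission value.

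**Conclusion.** The contradiction is real but narrow. As worded, the time factor and post hoc comparisons give total weight gain since admission, whereas the aim and the outcome concern gain after discharge. This is a mismatch between the quantity estimated and the quantity defined, not a bias in the randomised comparison of total gain.

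The only quantified harm is possible noise: power of .54 to .36 in place of .56, for an assumed d of 0.5, an assumed 40 v 20 contrast at alpha .10, an assumed SD ratio of 0.25 to 1, and independence. A negative correlation would reduce or remove the loss. Because baseline assessment may follow admission by some days (screening takes place in the first 48 to 72 hours), the inpatient gain counted may also be less than that of the whole stay.

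The ambiguous initial contrast needs defining, and the growth-model wording should be aligned for consistency. The point merits correction because the weight result could feed the scale-up decision and the correction is cheap; it does not touch the primary feasibility outcomes.

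**What to change.** For weight only:

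1. Make discharge (T2) the reference in the initial and post hoc contrasts, and state that the prefix in the initial contrast means pre-discharge for weight.
2. In the growth model, set time zero at discharge, with loadings in elapsed weeks (about 0, 4, 13 and 26) and admission weight as a covariate instead of the first occasion. A piecewise model with separate inpatient and post-discharge slopes is an acceptable alternative.
3. Because discharge weight is post-randomisation, report admission-to-discharge gain and length of stay by arm, so that an arm difference arising in hospital can be seen.

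Leave baseline as the reference for accommodation, which has no discharge measurement.

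The cost is analysis wording and one fewer occasion for weight in the four-wave version. No new data are needed, since Table 4 already schedules weight at discharge and at each follow-up. If weight leaves the common five-occasion MANOVA, say so explicitly.
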